### Study design

This cluster randomized trial utilizes a 2 × 2 factorial design [48] to assess the impact of S&D reduction training and the YWHC intervention, resulting in four study conditions: (1) Clinic S&D reduction training + PrEP/SRH + YWHC, (2) Clinic S&D reduction training + PrEP/SRH only, (3) No Clinic S&D reduction training +PrEP/SRH + YWHC, (4) No Clinic S&D reduction training + PrEP/SRH only (Fig. 1).

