### Randomization

Stratified randomization was conducted via SAS Software after clinic selection was finalized. The sample of 12 clinics was first grouped into three strata (peri-urban/city, peri-urban/provincial, and semi-rural/provincial) based on geographic location type (peri-urban vs. semi-rural) and clinic administration type/jurisdiction (city vs. provincial), with four clinics in each stratum. Within each stratum, clinics were then randomly assigned to study conditions based on a 1:1:1:1 allocation. Because there may be important differences pertinent to the outcomes that cannot be made homogenous, such as geographical region, stratified randomization was conducted to achieve even distribution of these factors across study arms. This reduces variability in the estimation of the intervention effect, with resulting increases in power/precision of estimates [49].

The six clinics randomized to receive the S&D reduction training will participate in workshops aimed to reduce clinic staff’s S&D attitudes and behaviors toward AGYW. For the 6 clinics randomized to the YWHC, AGYW participants recruited from communities in clinic catchment areas will be asked to participate in two workshops.

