#### AGYW level

The testing of Aim 3 will be done by intention to treat analysis, examining the effects of intervention groups at both levels (clinic and individual) on PrEP readiness, uptake and adherence. PrEP uptake will be defined as any use of PrEP. We will consider both short-term uptake within the first 3 months after study enrollment and uptake at any point during the 9-month follow-up period. Initially, we will calculate the proportion of AGYW with any use of PrEP, overall, and within each study arm, calculating 95% confidence intervals using the binomial distribution. Given the need to consider the influence of the cluster randomization by clinic, we will use generalized estimating equations (GEE) [61] models with a logit link and an exchangeable correlation structure to estimate the effects of randomization groups on both short-term (3-month follow-up) and long-term follow-up period (9-month follow-up). Models will include both intervention groups (i.e., S&D reduction training and YWHC) as covariates. Effects of clustering by randomization clinic may be examined by adjusting the variance by the inflation factor [1 + (m-1)r], where *m* is the average clinic size and *r* is the interclass correlation estimate. If the Hausman assumption of correlation between the random and fixed effects is violated, then we may include fixed effects representing cluster identification.

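### The optional switch to clinic fixed effects cannot estimate either Aim 3 intervention effect, because both interventions are allocated by clinic

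*Protocol article*

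**What the plan says.** Under Study design, the protocol article states: "This cluster randomized trial utilizes a 2 × 2 factorial design". Under Randomization, the 12 clinics form three strata of four, and "clinics were then randomly assigned to study conditions based on a 1:1:1:1 allocation". The same section gives the resulting split. For the training: "The six clinics randomized to receive the S&D reduction training will participate in workshops". For the behavioural intervention: "For the 6 clinics randomized to the YWHC, AGYW participants recruited from communities in clinic catchment areas will be asked to participate".

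Under Analysis, AGYW level, the committed uptake model is a GEE with logit link and exchangeable correlation, fitted at 3 and 9 months. Its treatment terms are given as: "Models will include both intervention groups (i.e., S&D reduction training and YWHC) as covariates". The same paragraph ends with the contingency at issue: "If the Hausman assumption of correlation between the random and fixed effects is violated, then we may include fixed effects representing cluster identification".

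The rest of that section says that adherence will be approached much as uptake is, using generalised linear mixed models, and that secondary outcomes will be handled along similar lines. Baseline covariates may be added if the arms look different descriptively.

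**The concern.** A clinic fixed effect absorbs everything that is constant within a clinic. S&D training is constant within a clinic because the clinic receives it. YWHC is delivered to individual women but allocated by clinic, so it is constant within a clinic too. The section's reference to effects at clinic and individual level describes delivery, not allocation. Once the contingency is invoked, the model keeps no information on either randomised comparison.

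What is at stake is whether the contingency can answer Aim 3 at all. The cross-references carry it beyond uptake to adherence and the secondary outcomes. The adherence models are mixed models, in which a Hausman-type check could at least be attempted on other covariates.

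**Working it through.** **Where the planned information lies.** The article gives no figure for the fallback. The nearest is its detectable difference of 9 to 13% (Sample size and power). The stated inputs are 12 clusters of 75, 10% attrition, ICC 0.01, two-sided 5% and 80% power.

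- Analysed per clinic: 75 × 0.9 = 67.5.
- Design effect: 1 + (67.5 − 1) × 0.01 = 1.665.
- Effective number per side, six clinics against six: 6 × 67.5 / 1.665 = 405 / 1.665 = 243.2.
- Detectable difference d, two-proportion normal approximation: d = [1.96·√(2p̄(1−p̄)) + 0.842·√(p₁(1−p₁) + p₂(1−p₂))] / √243.2, with p₂ = p₁ + d and p̄ their mean.

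The article gives no control proportions, so p₁ is an assumption, tried from 5% to 80%. The result is 7.1 points at 5%, 8.9 at 10%, 11.1 at 20%, 12.2 at 30%, 12.6 at 40% and at 50%, and 9.2 at 80%. The stated range is reproduced for control proportions of about 10% to 80%. It is therefore consistent with a comparison of six clinics with six, which is exactly the between-clinic information that clinic indicators remove.

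**Rank of the model.** Let C₁ to C₁₂ be the clinic indicators. Then:

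- S&D = the sum of Cₖ over the six trained clinics;
- YWHC = the sum of Cₖ over the six YWHC clinics.

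These are two exact linear dependencies, and the within-clinic variance of each intervention indicator is 0. With 12 clinics of 75 in three strata by four conditions:

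| Fixed part of the model | Columns | Rank | Main effects estimable? |
|---|---|---|---|
| Intercept, S&D, YWHC (planned) | 3 | 3 | Yes |
| Planned plus two stratum indicators | 5 | 5 | Yes |
| Clinic effects (intercept + 11, or 12 indicators), S&D, YWHC | 14 | 12 | No |
| The same plus the S&D × YWHC interaction | 15 | 12 | No |
| Three follow-ups pooled: 12 clinic, 2 time, S&D, YWHC | 16 | 14 | No |
| Three time points: 12 clinic, 2 time, 4 treatment-by-time | 18 | 18 | No; only changes over time |

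**What a forced fit returns.** One data set was simulated with 75 women per clinic, true log-odds ratios of 0.5 for each intervention and a clinic standard deviation of 0.18 on the logit scale. It was fitted with 12 clinic indicators in place of an intercept, and two indicators were removed to make the matrix invertible. Three different pairs gave the same log-likelihood, −606.05. The S&D coefficient was −0.03, 0.11 or 0.19, and the matching YWHC coefficient was 0.84, 0.41 or 0.46. In this coding the two printed coefficients are functions only of the observed log-odds in the two clinics left without an indicator. They are not intervention effects.

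**The trigger.** A Hausman comparison contrasts coefficients that the fixed-effects and random-effects models both estimate.

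- The exchangeable GEE has no random effect, so the check does not attach to the uptake model.
- In a mixed model, the intervention coefficients do not exist under fixed effects, so the check can respond only to other covariates.
- Clinics were randomised, so allocation is independent of the clinic effects by design. The condition that the check is meant to protect already holds for the two intervention terms.

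**The case against.** The strongest reply is that this is an unusable contingency and not a defect in the planned analysis. The sentence is conditional and says only that fixed effects may be included. The article commits to the GEE, which estimates both effects. A rank-deficient model usually shows itself when fitted, and the analyst would still have the pre-stated GEE. This stands, and it sets the severity.

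A second reply is that clinic fixed effects are not always fatal. For outcomes also measured at baseline, such as substance use, treatment-by-time contrasts remain estimable (18 columns, rank 18). This is true but does not rescue the sentence. Those contrasts are a different estimand from the effects at 3 and 9 months, and the AGYW-level section does not specify them. PrEP uptake after enrolment has no baseline value described. The difference-in-differences models belong to the clinic-level analysis of S&D training.

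Two stronger readings are tempting, and the article does not support them:

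- A reader might infer that the trial would report a contrast of single clinics with inflated type I error. That needs the check to fire, the option to be taken, the software to drop clinic indicators instead of the intervention terms, and the output to go unnoticed. The article makes none of these steps likely.
- A reader might infer from the preceding sentence that clustering is counted twice: "Effects of clustering by randomization clinic may be examined by adjusting the variance by the inflation factor". The article does not say that the factor multiplies GEE or mixed-model standard errors. It could equally be an alternative or a descriptive step, for example for the simple binomial intervals proposed earlier in the paragraph.

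**Conclusion.** The fallback is wrong as written. With clinic fixed effects in the main-effects model at 3 or 9 months, the matrix is two short of full rank (14 columns, rank 12), and neither S&D training nor YWHC has an estimable effect. This is exact and needs no assumption beyond allocation by clinic, which the Randomization section states. It does not depend on uptake, ICC or retention. The simulated coefficients only illustrate it. The check that would invoke the fallback is also unsuited to the purpose, since it cannot speak to the two randomised terms.

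It does not follow that the primary Aim 3 analysis is invalid. The committed GEE has full rank and is sound on this point. This is a should-fix correction to an optional step, and no sample size or power figure changes.

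**What to change.** Delete the sentence on the Hausman assumption and cluster fixed effects. Alternatively, limit it to fixed effects for the three randomisation strata, which leaves both interventions estimable (5 columns, rank 5).

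State that clinic enters as the clustering unit in GEE models or as a random effect in mixed models for every Aim 3 intervention effect, including the adherence and secondary outcomes that borrow the uptake approach. This need not exclude an S&D × YWHC interaction or other clinic-level covariates.

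The cost is a change of wording in the protocol and in any analysis plan that repeats the sentence. Sample size, data collection and trial conduct are unaffected.

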#### Sample size and power

For the AGYW analyses, the total sample size and number of clusters (clinic catchment areas) were selected to ensure sufficient power to detect meaningful differences in our primary outcomes, while also balancing considerations tied to reducing possible contamination (exposure to the intervention in control clusters) and implementation feasibility with a set number of clinics in the study area. Sample size estimates for tests of two proportions in a cluster-randomized design [56] were conducted for a 2-sided test with significance level of 0.05, power of .80, and intra-cluster correlation of 0.01 (based on our team’s past research in Cape Town communities), assuming 10% attrition over the 9-month follow-up period [52, 57]. This was not adjusted for multiple comparisons. Based on these parameters and calculations, the study sample includes 12 clusters (defined as clinics and their catchment areas), with a total sample size of 900 AGYW enrolled, 75 per cluster (clinic catchment area). This sample was chosen to ensure that meaningful differences in the primary outcomes of PrEP readiness, uptake, and adherence between groups would be detectable. We are powered to detect a difference between 9 to 13% in primary outcomes. Power analyses were first conducted in PASS software [58] and were refined in Stata [59] (see PrEPARE Additional Power Calculation Information in Supplementary File 4).

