#### Clinic level

AGYW service utilization will be assessed and analyzed through clinic level data at each of the 12 study clinics during an 8-month period pre- and post-training (e.g., HIV testing; number of PrEP prescriptions). Baseline and follow-up clinic staff surveys will be analyzed to examine changes in attitudes and stigma at the clinic level. Initial analyses will be descriptive and evaluate group differences comparing intervention and control clinics using unpaired t-tests with unequal variance or nonparametric tests, as appropriate. Using multilevel modeling approach, we will investigate and account for clustering at the clinic level. We will use difference-in-differences (DD) methods as done in another South African study to examine utilization of services by AGYW and staff attitudes and behaviors in the 8 months between intervention and control clinics [60]. The DD estimator reflects the average change in clinics that received S&D reduction training, after the average change in utilization in control clinics is subtracted, assuming parallel trends in clinics over time had the S&D reduction training not been implemented. DD estimates will be calculated for each outcome separately; models will include covariates for time (pre- vs. post-intervention), treatment (training vs. no training) and an interaction between the two. The clinics identified are similar in size, services, and populations served. Any clinic features for which we cannot achieve balance through the design will be included as covariates in the multivariable DD analyses. A stigma score will constitute one primary outcome for these analyses. To examine short-term changes between pre-intervention and 4-month follow-up, DD methods can be used to compare the average change in stigma scores in clinics that received S&D reduction training, removing any changes observed in control clinics. We will use generalized estimating equations (GEE) [61] to examine provider-level stigma scores measured at 4- and 8-month follow-up comparing trained and untrained clinics, accounting for clustering at the clinic-level.

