Finally, we will include additional baseline covariates in the models, including sociodemographic factors and behavioral risks, should initial descriptive analyses suggest differences in the distribution of these factors across study arms. In subsequent exploratory analyses, we will examine the potential mediating and moderating roles of key behavioral, social, and structural factors hypothesized to influence PrEP uptake (e.g., social support; economic dependence), as outlined in Outcomes. To assess adherence in the past month, we will measure drug-level concentration, TFV-DF assessed through DBS samples, at 3, 6 and 9 months. The threshold for adherence will be established based on recommendations from ongoing studies and research designed to inform thresholds in women. Secondary adherence measures will include self-reported use, which will be examined as the number of days in the past 30 days when PrEP was taken. Using clinical/pharmacy data on PrEP dispensation and self-report of months in which PrEP was used, we will examine adherence (the number of months of PrEP use) and discontinuation. Initially, we will examine differences in the proportions of AGYW who are adherent at months 3, 6, and 9 in each study arm, calculating confidence intervals using a binomial distribution. Our analytic approaches will be similar to those described for uptake. We will use generalized linear mixed models to allow for multiple variance components, including clustering of clinics and repeated measures of adherence within individuals over time. We will use logit, Poisson, and linear regression approaches, as appropriate.

Analyses of secondary outcomes will use similar analytic approaches and examine hypotheses tied to intervention effects on behavioral risk endpoints (e.g., substance use) and on AGYW’s assessment of stigma (e.g., participants attending the S&D reduction trained clinics will report lower levels of stigma from clinic staff than participants who attend the non-trained clinics). Other model specifications, such as zero-inflated Poisson or negative binomial will be considered for count outcomes (e.g., the number of condomless sex acts) that have excess zero values or overdispersion.

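### Baseline covariates enter the AGYW outcome models when the arms look different, instead of from a short prognostic list fixed in advance

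*Protocol article*

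**What the plan says.** **AGYW level.** Under Analysis, AGYW level, the GEE models for PrEP uptake contain indicators for the two interventions. Sociodemographic factors and behavioural risks measured at baseline are added "should initial descriptive analyses suggest differences in the distribution of these factors across study arms". Two broad classes are named, and the trigger is observed imbalance. Adherence and the secondary outcomes are to be analysed in a similar way.

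**Other routes for covariates.** The paragraph on missing data separately adds demographic covariates as proxies for dropout. It does not name them and attaches no balance condition.

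**Strata.** Under Randomization, 12 clinics were grouped into three strata of four by location and jurisdiction, and within each stratum "clinics were then randomly assigned to study conditions based on a 1:1:1:1 allocation". The models described do not include these strata.

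**Clinic level.** Baseline is used through DD: "The DD estimator reflects the average change in clinics that received S&D reduction training", net of the change in control clinics. A parallel covariate rule reads "Any clinic features for which we cannot achieve balance through the design will be included as covariates in the multivariable DD analyses".

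**The concern.** Covariate adjustment in a randomised trial earns its keep through prognosis. A covariate that predicts the outcome improves precision whether or not it is balanced, and one that does not predict the outcome adds nothing even if it is imbalanced. A rule that looks at balance selects on the wrong property.

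Three consequences follow from the rule as written.

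- A strong predictor that happens to balance is left out, and its precision gain is lost.
- The strata, which were used to randomise and are known in advance, are not brought in by it.
- The model behind the primary result is settled only after the baseline data have been inspected by arm. A later analysis plan could add a list and a threshold, but the trigger would still be observed imbalance. This is a stated rule, not a detail left open.

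**Working it through.** **1. The plan's own figure.** Inputs from Sample size and power: "2-sided test with significance level of 0.05, power of .80, and intra-cluster correlation of 0.01"; "assuming 10% attrition over the 9-month follow-up period"; "12 clusters (defined as clinics and their catchment areas), with a total sample size of 900 AGYW enrolled, 75 per cluster". Allocation gives 6 v 6 clinics for each main effect.

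- Analysed per clinic: m = 75 × 0.9 = 67.5.
- Design effect: 1 + (67.5 − 1) × 0.01 = 1.665.
- Effective n per side: 6 × 67.5 / 1.665 = 405 / 1.665 = 243.2.

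Solving the two-proportion formula for 80% power gives these detectable differences:

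| Control proportion (assumed) | Detectable difference |
|---|---|
| 0.10 | 8.9 points |
| 0.20 | 11.0 points |
| 0.40 | 12.6 points |
| 0.45 | 12.7 points |

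This agrees with "We are powered to detect a difference between 9 to 13% in primary outcomes". The stated figure reproduces for the main-effect comparison without covariates.

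**2. What the trigger costs.** The documents give no R2 and no imbalance criterion, so both are assumed. The simulation had 10,000 trials per setting, 12 clinics of 68, 6 v 6, and a continuous outcome:

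y = effect × arm + √R2 × x + √(1 − R2) × (clinic effect + residual)

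The outcome ICC was 0.01 and the covariate ICC 0.02 (assumed). Analysis was a t test on clinic means with 10 df. The adjusted version used y − b·x, with b the within-clinic slope. The trigger was an individual-level two-sided 5% test of x between the two sides. The true effect was 0.26 SD.

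| R2 (assumed) | Power: never adjust | Only if imbalanced | Always adjust | Type I error, only if imbalanced |
|---|---|---|---|---|
| 0.05 | 73% | 74% | 77% | 4.9% |
| 0.10 | 73% | 75% | 78% | 4.3% |
| 0.20 | 71% | 74% | 83% | 4.0% |
| 0.30 | 69% | 74% | 87% | 3.6% |

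Type I error with fixed adjustment was 5.1 to 5.5%. The trigger fired in about 20% of trials although allocation was random, because clinics and not individuals are randomised. A repeat run at R2 0.10 and 0.20 agreed to within about one percentage point.

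**3. What the strata cost.** With an intercept and two factors, 12 clinics leave 12 − 3 = 9 df. Two stratum terms leave 7. For 10% v 19%:

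- Non-centrality: 0.09 / √[(0.10 × 0.90 + 0.19 × 0.81) / 243.2] = 2.84.
- Power by the non-central t: 71.6% on 9 df and 68.5% on 7 df, if the strata explain nothing. Any between-clinic variance that they explain works against this loss.

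**4. Clinic level, as a check on how far the point reaches.** With baseline/follow-up correlation rho between clinic means, the large-sample variances are 2(1 − rho) for DD and 1 − rho² for ANCOVA, so the ratio ANCOVA/DD is (1 + rho)/2. That formula ignores estimating a slope from 12 clinics. Simulating ANCOVA on the baseline mean, both factors and strata gives:

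| rho (assumed) | Large-sample ratio | Ratio with 12 clinics |
|---|---|---|
| 0.3 | 0.65 | 0.79 |
| 0.5 | 0.75 | about 0.9 |
| 0.6 to 0.7 | 0.80 to 0.85 | about 1.0 |
| 0.8 | 0.90 | 1.07 |

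Power for an effect of 1.8 SD of clinic means, DD v ANCOVA, was 63% v 72% at rho 0.3, 85% v 85% at 0.6 and 99% v 97% at 0.8.

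**The case against.** **The power loss is small at modest R2.** This stands: 74% v 77% at 0.05 and 75% v 78% at 0.10. The gain is worth having because it costs little, not because the trial fails without it.

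**The rule is not the only route for covariates.** This also stands. Demographic covariates enter as dropout proxies without a balance condition, so age might be adjusted for anyway. But they too are unnamed, and they serve a different purpose.

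**The list and criterion belong in an analysis plan that is not shown.** This holds for the list and the threshold, but not for the choice of imbalance as the trigger, which the article states.

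Four stronger readings might be inferred and are not supported.

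- *That the rule inflates type I error.* Simulation gave 3.6 to 4.9%, which is conservative, though for one covariate and a fixed criterion.
- *That some imbalance is near certain to be flagged.* High flag rates need an assumed test, threshold and number of covariates; the article states none of these.
- *That the baseline value of the main outcome is being discarded.* Uptake is any PrEP use after enrolment, and dried blood spots are collected at follow-up from those reporting PrEP use. Neither has a useful baseline. The questionnaire does cover substance use and victimization.
- *That DD is an error to be replaced.* Randomisation makes parallel trends hold in expectation, so DD is unbiased. It loses precision to ANCOVA only at low rho, and the documents give no rho. The clinic-feature rule can also be read as covering features that stratification did not handle, which are knowable at randomisation.

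**Conclusion.** The point holds for the AGYW models. Selecting baseline covariates by observed imbalance forgoes precision and leaves the final model to be settled after the data by arm have been seen. On the assumptions in the working (one covariate, continuous outcome, a 5% trigger), the shortfall in power against always adjusting is about 3 to 4 percentage points at R2 of 0.05 to 0.10, 9 points at 0.20 and 13 points at 0.30. None of these R2 values comes from the documents. For PrEP uptake and dried-blood-spot adherence, the gain rests on the strata, age and any other pre-named predictor, and may be at the low end.

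The validity of the test is not in question, and the stated detectable difference of 9 to 13% is unaffected. At clinic level no change is required: with 12 clinics, ANCOVA is more precise than DD only if rho is below about 0.6.

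**What to change.** In the AGYW-level section and the analysis plan:

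1. Drop the imbalance trigger for the primary AGYW models.
2. Always include a short list fixed now, whatever the observed balance: the three randomisation strata, age, and the baseline value of the outcome where it is measured (for example substance use or victimization, but not PrEP uptake or dried-blood-spot adherence).
3. Name the demographic covariates used as dropout proxies.
4. Keep imbalance-driven adjustment as a sensitivity analysis.

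At clinic level DD may stay. ANCOVA on the baseline clinic mean is an optional alternative, most plausible for stigma scores, where unlinked surveys and staff turnover may make rho low.

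**Cost.** Wording only; the article gives the trial status as recruiting. There are two statistical costs. The strata use two cluster-level df (9 to 7, or 71.6% to 68.5% power in the worked case if they explain nothing). With a logit link, the odds ratio becomes conditional on the listed covariates, which the report should say.
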